A process evaluation will be conducted to understand the mechanisms underlying the effectiveness and to ensure generalizability of intervention effectiveness [7, 8]. Therefore, the process evaluation will explore which components of the programs and which contextual factors contribute to the effects. This knowledge is essential for building an evidence base that informs policy and practice [9]. The process evaluation will focus on the role of networks of ambulatory practices in Germany (‘Arztnetze/Praxisnetze’), in which the ARena project is embedded. These practice networks organise quality improvement and additional reimbursement for specific activities for participating ambulatory practices. Exploring the impact of those networks on antibiotic prescribing is of particular interest. The networks may enhance the contagion of new ideas and practices through various mechanisms of social influence between participating healthcare providers and thus enhance the contagion of knowledge and practices [10]. Reducing antimicrobial resistance is only possible if the large majority of physicians join efforts to reduce antibiotic prescribing. The context of a sustained network may influence physicians’ willingness to cooperate with programs such as ARena because the repeated interaction in the network enhances mutual trust and facilitates the exclusion of non-cooperators [11].

The planned study has three central aims: (a) to determine and compare the effectiveness of three implementation programs to optimise antibiotic prescribing in ambulatory care, (b) to compare the outcomes of the three implementation programs with standard care and (c) to provide insight into the fidelity of the implementation programs, their potential working mechanisms and the impact of health system-related factors on outcomes.

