### Randomisation procedure

The allocation to the three arms of the study is done by the study statisticians, using a computer program, and concealed from all others in the project. The 14 practice networks are allocated to one of the three intervention arms under the constraints that the arms contain a similar number of practices (not more than one practice difference) based on an estimated participation rate of practices within the networks and that intervention arm A contains 4 practice networks and intervention arms B and C each 5 practice networks. From a total of 34,650 possible allocation outcomes, 112 meet this requirement, from which a computer program randomly picks one.

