### Data analysis

#### Outcome evaluation

The primary objective of this study is to examine the change of the antibiotic prescription rate in targeted patients within three intervention arms and the comparison between the three intervention arms. The confirmatory analysis of the primary endpoint will be conducted on the basis of the Intention-To-Treat (ITT) population where all patients will be included in the analysis and assigned to the group they were randomised to.

To account for multiple testing and to assure a global significance level of 5%, a multiple test procedure for hierarchically ordered hypotheses will be applied. In the first stage, differences regarding the primary endpoint (prescription of antibiotics) before and after the intervention in intervention groups B and C are tested. To assure a significance level of 5% within the first level, the hypotheses for the pre- and post comparison will be tested at a local significance level of 5/2%. The second step includes the pre-and post comparison in intervention group A. The significance level of the rejected hypotheses from step one is taken (2.5% if only one hypothesis can be rejected, 5% if both hypotheses can be rejected). If significance is reached in intervention groups A and B, differences between groups A and B will be tested at a local significance level of 5/2%. Similarly, difference between groups A and C will be only tested if significance is reached for groups A and C in the steps 1 and 2. If the hypotheses in step 1 or 2 cannot be rejected, the group comparison will not be tested primarily.

In all stages described above, a logistic mixed effects model will be applied to assess the respective hypotheses regarding the primary endpoint. In the first and second stage, the time (before/after the intervention) is included as fixed effect. A random intercept will be included for patients and for practices. For the comparisons in the third stage, the intervention group will be included as fixed effect additionally. Furthermore, age and gender will be included as covariates. Finally, sensitivity analyses will be conducted using different populations (per protocol population where patients with major protocol violations are excluded and appropriate subgroups). Since all these analyses are based on claims data, missing values cannot be tracked.

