### Sample size calculation

The sample size calculation is based on the expectation to find an absolute reduction of the antibiotic prescription rate in targeted patients from 61 to 50% in intervention group A and from 61 to 45% in groups B and C. Thus, the effect is expected to be 5% higher in the enriched intervention groups B and C compared to intervention group A.

To control the overall type I error rate at 0.05 (two-sided), a hierarchical 3-step testing procedure will be applied. In the first step, the hypotheses of no difference between the pre- and post prescription rate in group B and C will be tested. If at least one of these hypotheses can be rejected, the hypothesis of no difference in the pre- and post rate in group A will be tested. If, additionally, this hypothesis can be rejected, the hypotheses of no difference between the post rates of groups A and B as well as groups B and C will be tested. The sample size is calculated based on chi-squared tests assuring a (global) power of 80% for the rejection of all the above described, hierarchically ordered hypotheses. Furthermore, to take the clustered structure into account, an intra-cluster correlation coefficient (ICC) for patients in practices of 0.05 and of 0.7 for cases clustered in patients is assumed. Together with the above described expected pre- and post prescription rates in the three groups, this results in a sample size of 23,933 patients in group A, 11,967 patients in group B and 11,967 patients in group C. With an average practice size of 80 patients per quarter this leads to 75 practices in group A, 38 practices in group B and 38 practices in group C.

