## Discussion

The evidence base of large scale programs to reduce antibiotic prescribing in acute non-complicated infections in primary care is limited, so this project can provide an important contribution. Nevertheless, a number of limitations of the study should be acknowledged. The study is randomised, but the number of units for allocation (i.e. networks) is small, leaving room for bias. Primary and secondary outcomes are based on claims data, which have inherent limitations and strengths. Given the multifaceted programs, it will be difficult to separate out the impact of various program components. On the other hand, strong aspects of the program are its large scale and closeness to daily practice. The focus on practice networks and implementation outcomes, which will be explored in the process evaluation, adds value to the study. The analysis of components of the complex implementation programs, using the TIDier checklist, contributes to the transparency of the implementation programs.

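### Networks are randomised, but the confirmatory model and the sample size leave out the network level, so any positive network variance takes the A–B and A–C tests above 2.5%; how far depends on a network ICC the protocol does not give

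*Protocol article*

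**What the plan says.** Under Randomisation procedure, the allocated unit is the network: "The 14 practice networks are allocated to one of the three intervention arms", with the constraint that "intervention arm A contains 4 practice networks and intervention arms B and C each 5 practice networks".

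Under Data analysis, Outcome evaluation, one logistic mixed effects model serves all stages of the hierarchical test: "A random intercept will be included for patients and for practices". In the last stage, "For the comparisons in the third stage, the intervention group will be included as fixed effect additionally"; no network term is added there either. On the level, "differences between groups A and B will be tested at a local significance level of 5/2" per cent, and A–C is handled in the same way.

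Under Sample size calculation, "an intra-cluster correlation coefficient (ICC) for patients in practices of 0.05 and of 0.7 for cases clustered in patients is assumed". No ICC for practices within networks appears. That section describes the last stage as a comparison of post-intervention rates.

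Two other places bear on whether network variance can be taken as zero. The Background says "The networks may enhance the contagion of new ideas and practices through various mechanisms of social influence between participating healthcare providers". The Discussion concedes that "the number of units for allocation (i.e. networks) is small, leaving room for bias".

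**The concern.** The arm is a property of the network. Arm A has 4 independent replicates and arms B and C have 5 each. A model whose highest random level is the practice treats roughly 64 practices per arm (193/3 ≈ 64.3) as independent replicates. If practices in one network resemble each other more than practices in different networks, the standard error of an arm contrast is too small.

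A–B and A–C are the confirmatory comparisons that rest on the randomisation; the earlier stages are before-after comparisons within an arm. A chance difference between a handful of networks could be read as the effect of an enriched programme, and the claim of a 5% global level would fail at the step where randomisation matters most.

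**Working it through.** **1. Does the stated sample size contain a network component?** Inputs from Sample size calculation: post rates of 50% (A) and 45% (B), 80% power, a 2:1 patient ratio, ICCs of 0.05 and 0.7, and 80 patients per practice per quarter. The local 2.5% level is from Outcome evaluation.

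- Pooled rate: (0.50 + 0.5 × 0.45)/1.5 = 0.4833.
- Unadjusted n in A: [2.2414·√(3 × 0.4833 × 0.5167) + 0.8416·√(0.25 + 0.2475/0.5)]²/0.05² = (1.9400 + 0.7264)²/0.0025 = 2,844.0.
- Design effect: (1 + 79 × 0.05) × (1 + 0.7) = 4.95 × 1.7 = 8.415. The factor 1.7 (two cases per patient) is inferred from the fit; the protocol does not state it.
- A: 2,844.01 × 8.415 = 23,932.4, stated 23,933. B: 11,966.2, stated 11,967.

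The plan's figures are reproduced with practice and patient terms alone, so the network level is absent from the sample size.

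**2. Type I error of A–B at the nominal 2.5%.** Assumptions: post rates are compared; the total between-practice ICC is 0.05, of which ρ lies between networks; there are 320 cases per practice (80 × 4 quarters, consistent with 23,933/75 ≈ 319); the patient factor is 1.7. The protocol gives no ρ, so a range is shown. Let h = 1/K_A + 1/K_B for K_A and K_B practices. In units of p(1−p):

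- Variance the model sees: (0.05 + 0.95 × 1.7/320)·h = 0.05505·h.
- Actual variance: 0.05505·h + ρ·(1/4 + 1/5 − h).
- Actual type I error: 2·[1 − Φ(2.2414/√R)], where R is the ratio of actual to modelled variance.

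Two arm sizes are shown because the documents point to both: 64/64 from 193 practices with near-equal arms (h = 0.03125), and 75/38 from Sample size calculation (h = 0.03965).

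| ρ | SE ratio, 64/64 | Type I error, 64/64 | SE ratio, 75/38 | Type I error, 75/38 |
|---|---|---|---|---|
| 0 | 1.00 | 2.5% | 1.00 | 2.5% |
| 0.001 | 1.12 | 4.4% | 1.09 | 4.0% |
| 0.002 | 1.22 | 6.6% | 1.17 | 5.6% |
| 0.005 | 1.49 | 13.2% | 1.39 | 10.8% |
| 0.01 | 1.85 | 22.6% | 1.70 | 18.7% |
| 0.02 | 2.42 | 35.5% | 2.18 | 30.4% |

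A–C has the same 4-versus-5 structure. Simulated practice means (64/64, 40,000 runs per value) gave similar rates: 4.6%, 13.8% and 24.3% at ρ = 0.001, 0.005 and 0.01. A network-level t test on the same data stayed at 2.1–2.6%. The binary logistic mixed model itself was not simulated.

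**3. Degrees of freedom.** At 2.5% two-sided the critical value is 2.24 (normal), 2.84 (t, 7 df: 4 + 5 − 2) or 2.59 (t, 11 df: 14 − 3). Using 2.24 with a correct network-level standard error would still reject in 6.0% (7 df) or 4.7% (11 df) of trials under no difference.

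**4. Power of A–B at the stated N.** The planned variance is 0.2497 × 8.415 × (1/23,933 + 1/11,967) = 0.000263 (SE 0.0162). Add 0.2497 × ρ × 0.45 and test the 5-point difference with 7 df. Power is 61% at ρ = 0, 45% at 0.001, 21% at 0.005 and 13% at 0.01. The planned normal approximation without a network term gives 80%.

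**The case against.** **The size is assumed.** A reader might infer that A–B and A–C reject far above 2.5% as a matter of fact. The protocol does not support that: it states no network ICC, and at 0.001 the excess is modest. The Background says only that networks may spread practices, as motivation for the process evaluation. Only the direction is certain. This objection stands.

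**Not every stage is affected alike.** A reader might also infer that all stages share this inflation. In the within-arm pre-post tests a stable network effect largely cancels, and only network-by-period variation is left unmodelled. The same would hold if stage 3 compared change, which the stated primary objective could suggest. This stands as a limit on the figures above. However, the stage 3 model as described adds a group term and no group-by-time term, and the sample-size section compares post rates.

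**The analysis plan may repair it.** Methods for degrees of freedom and sensitivity analyses are commonly left to the SAP, and their absence is not the finding. The random effects were not deferred: the protocol names them and omits the randomised level.

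**Gatekeeping or constrained allocation protects stage 3.** Neither does. With the planned falls of 11 and 16 points, the pre-post tests have over 99.9% power under the protocol's own design effect, so stage 3 is almost always reached. The allocation constraint balances numbers of practices, not prescribing.

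**The limitation is already conceded.** The Discussion mentions the few allocation units as a source of bias. It does not address the standard error, and the model is unchanged.

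**Conclusion.** The mismatch holds. Networks are randomised, and neither the confirmatory model nor the sample size has a network component. For any positive network variance, A–B and A–C exceed their 2.5% level, and the 5% global level and 80% power do not hold as stated.

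The size is conditional on the network ICC and on a comparison of post rates: roughly 4% at 0.001, 11–13% at 0.005 and 19–23% at 0.01, across the two readings of arm size. At 0.005, one tenth of the protocol's own practice ICC, the error is already more than four times nominal. These figures also rest on the inferred 320 cases per practice and factor 1.7. They do not apply to the within-arm stages or to a comparison of change. It should be corrected before analysis, because the affected tests are the randomised ones.

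**What to change.** In Data analysis, Outcome evaluation: add a random intercept for network and, where time is in the model, a network-by-period effect. Test A–B and A–C with small-sample degrees of freedom at network level, about 7 for a two-arm model or 11 for a three-arm model.

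In Sample size calculation: state the network ICC assumed, with a range, and restate the A–B and A–C power with that level included. No extra enrolment is asked for.

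A permutation test over the admissible allocations is a natural suggestion, but it should not be adopted yet. The stated 34,650 possible allocations equals 12!/(4!·4!·4!), whereas 14 networks split 4/5/5 give 14!/(4!·5!·5!) = 252,252, so the admissible set must first be corrected. With arm C held fixed, a p-value of 2.5% also needs at least 1/0.025 = 40 admissible A/B splits, and the constraint may leave fewer.

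Cost: changes to the model specification and a restated power figure, with no new data. Intervals for A–B and A–C become wider, and the honest power at the stated N is clearly lower: about 61% at network ICC 0, 45% at 0.001, 21% at 0.005 and 13% at 0.01 with 7 df.

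### As written, the third-stage model (time plus group, no interaction) estimates an arm difference pooled over the before and after periods, not the post-rate difference the trial was sized for

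*Protocol article*

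**What the plan says.** The outcome evaluation part of the Data analysis section applies a logistic mixed effects model at every stage of the hierarchical procedure. "In the first and second stage, the time (before/after the intervention) is included as fixed effect". Then: "A random intercept will be included for patients and for practices". For the comparisons between arms: "For the comparisons in the third stage, the intervention group will be included as fixed effect additionally". Age and gender are added as covariates. No group-by-time term, adjustment for the practice's baseline rate or restriction to post-intervention data is stated. On the level of the test, the same section says that "differences between groups A and B will be tested at a local significance level of 5/2" per cent, and it treats A vs C likewise.

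The Sample size calculation section defines the third step on a different quantity: "the hypotheses of no difference between the post rates of groups A and B as well as groups B and C will be tested". The planned rates are 61 to 50% in A and 61 to 45% in B and C, so the arms are assumed equal before the intervention and 5 points apart after it.

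**The concern.** In a model with main effects of time and group only, one group coefficient serves both periods. The data before the intervention, where no difference is expected, pull it towards zero. It answers neither the question in the sample size section (do the post rates differ?) nor the other natural question (do the arms change by different amounts?).

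At stake is the confirmatory comparison of the enriched programmes with the standard one, part of the study's first aim. A true 5-point advantage would be tested through a diluted contrast at a size calculated for the undiluted one. A difference already present before the intervention also goes into the coefficient. This matters because only 14 networks are randomised, and the allocation constraint balances practice numbers, not baseline prescribing.

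**Working it through.** **1. What the trial was sized for.** Inputs from the Sample size calculation section: post rates 0.50 (A) and 0.45 (B), two-sided testing, 80% power, 80 patients per practice, ICC 0.05 and 0.7, twice as many patients in A as in B. The local level of 2.5% comes from the Data analysis section. Two cases per patient is my inference; the article does not state it.

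With r = nB/nA = 0.5 and p̄ = (0.50 + 0.5 × 0.45)/1.5 = 0.4833:

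nA = [2.2414 × √(p̄(1−p̄)(1+1/r)) + 0.8416 × √(0.50×0.50 + 0.45×0.55/r)]² / 0.05² = 2,844.0

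Design effect = (1 + 79 × 0.05) × (1 + 1 × 0.7) = 4.95 × 1.7 = 8.415

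2,844.0 × 8.415 = 23,932.4, and half of it is 11,966.2. Rounded up, these are the stated 23,933 and 11,967. The plan's figure is therefore reproduced as a comparison of post rates, 50% vs 45%.

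**2. What the stated model estimates.** The post-period log OR is ln(0.45/0.55) − ln(0.50/0.50) = −0.201 (OR 0.82). I fitted logit(p) = b0 + b1·time + b2·group to the planned cell rates (A: 0.61, 0.50; B: 0.61, 0.45), with twice as many patients in A:

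| Pre:post data | b2 (log OR) | OR | Share of −0.201 |
|---|---|---|---|
| 1:1 | −0.102 | 0.90 | 51% |
| 1:2 | −0.136 | 0.87 | 68% |
| 2:1 | −0.069 | 0.93 | 34% |

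With equal arms the 1:1 value is −0.103, so allocation hardly matters. In percentage points, for equal periods: (61+50)/2 = 55.5 against (61+45)/2 = 53, a difference of 2.5 instead of 5. With a group-by-time term the same rates give a baseline group log OR of 0 and an interaction of −0.201.

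These are marginal odds ratios, without random effects. The planned model gives conditional ones, which differ in size but not in direction.

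**3. What this does to power.** I give each period the effective size behind the plan's own calculation (about 2,845 in A and 1,422.5 in B) and the same standard error s. From the post rates, s = √(0.25/2,845 + 0.2475/1,422.5) = 0.0162, which gives 80% power for 5 points. The correlation ρ between an arm's pre and post results is not in the document, so I show a range.

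- Pooled contrast: Φ(0.025 / (s√((1+ρ)/2)) − 2.2414)
- Interaction: Φ(0.05 / (s√(2(1−ρ))) − 2.2414)

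| ρ | Pooled (as written) | Interaction |
|---|---|---|
| 0 | 48% | 48% |
| 0.3 | 37% | 64% |
| 0.5 | 32% | 80% |
| 0.7 | 29% | 96% |
| 1 | 24% | – |

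Put differently, the formula of step 1 for 55.5% vs 53% requires 11,314 in A before the design effect, against 2,844: about four times as many.

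**4. Baseline differences.** Let both arms change equally on the logit scale, with A going from 61 to 50%. If B starts 3 points lower, at 58%, it ends at 46.9%, and the group OR is 0.88 although the programmes do not differ. A gap of 2 points gives 0.92, and a gap of 5 points gives 0.81, about the whole planned effect. The interaction OR is 1.00 in each case. An unadjusted post-rate comparison gives the same 0.88 for the 3-point gap (46.9% vs 50%).

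**The case against.** The strongest reply is that the article is a condensed text, announces a detailed statistical analysis plan, and says that the model assesses the respective hypotheses. On that view the sentence names a factor rather than a full equation, and the post-rate contrast is understood. It is true that the article does not exclude an interaction and that the analysis plan may add one. But the article does list the fixed effects of its confirmatory model, and following that list does not test its own hypothesis. A reading on post-intervention data alone fits poorly, because group is added to a model that contains time, and time would be constant in such data. If that reading was meant, the dilution disappears but baseline differences remain unadjusted.

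A reader might also infer more than the document supports:

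- *That the missing interaction causes baseline imbalance to be reported as a programme effect.* Step 4 shows that an unadjusted post-rate test carries the same gap. Under randomisation, chance differences between practices belong to the sampling error that the practice intercept is meant to cover, so omitting the interaction does not by itself inflate the type I error when the programmes are equal. The size of any imbalance between networks cannot be judged, because no network variance is given.
- *That the effect is halved as a matter of fact.* This needs about equal data in the two periods. The equal yearly patient numbers in the abstract suggest it, but the lengths of the before and after windows are not stated.
- *That a particular power figure applies.* Each one rests on a correlation and on effective sizes that the article does not give.
- *That difference in change is the stated target and the interaction the only remedy.* The objective is worded as change within arms plus comparison between arms, and the sample size section names post rates.

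**Conclusion.** The point holds for the model as written. The third-stage model and the third-stage hypothesis do not match, and this is a stated rule that needs correcting, not a detail left to the analysis plan. The group coefficient retains about half of the planned effect on the log-odds scale if the periods hold equal data, and 34% to 68% if one holds twice the data of the other. Power for A vs B is then well below the 80% used for sizing: 24% to 48% under the assumptions of step 3, with the exact loss unknown. The main harm is this dilution. Unadjusted baseline differences are a secondary concern, real with 14 networks but shared with any post-rate comparison that does not use the pre-period data.

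**What to change.** In the Data analysis section, add group-by-time to the third-stage model and name the confirmatory contrast for A vs B and for A vs C. Two contrasts would serve:

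1. The group difference in the after period, adjusted for the practice's pre-period prescribing rate. This keeps the hypothesis in the sample size section and deals with baseline differences between practices.
2. The group-by-time interaction, that is, the difference in change. The sample size section must then be restated to match.

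When the two sections are aligned, the pair of arms in the last comparison should be reconciled as well, since the sample size section names B and C where the analysis section names A and C.

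The cost is one model term or covariate; pre-period data are already needed for the first two stages. The price of the second option is power: under the approximation in step 3, the pure interaction has less power than the post-rate contrast if the pre/post correlation is below about 0.5. The choice should therefore be made, and its power checked, before the outcome data are seen.

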### Study population

Fourteen practice networks in two German federal states (Bavaria and North Rhine-Westphalia) are recruited for participation in the ARena project. For administrative reasons, the study will focus on patients insured by AOK health insurance, which are registered within a specific program for healthcare delivery (‘Besondere Versorgung’ as defined by German law § 140a SGB V a.F. bzw. § 140a Abs. 1. S. 2 Alt. 1 SGB V n.F). Compared to patients insured by other German health insurances, AOK-insured patients have somewhat lower income, less education, higher probability of migration background and lower self-reported health status [14]. On average, 35% of the population within the geographic reach of the participating practice networks in Bavaria are insured by AOK health insurance. At baseline, approximately 40,000 patients with AOK health insurance are registered in 193 participating ambulatory care practices in these 14 networks. In total, there are 304 eligible ambulatory care practices in these 14 networks. The patient population for the intervention arms will comprise patients who attended ambulatory practices for the following reasons: acute non-complicated infections of the respiratory tract (bronchitis, sinusitis, tonsillitis, otitis media), non-complicated cystitis and community-acquired pneumonia (CAP). The diagnoses will be based on physician-recorded ICD codes in administrative data, which are provided for reimbursement and lumped in 3-month periods.

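### The stage-three arm comparison omits federal state, which allocation does not balance, so any state difference in prescribing level passes into the A-B and A-C contrasts

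*Protocol article*

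**What the plan says.** All references are to the protocol article.

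- **Recruitment (Study population).** "Fourteen practice networks in two German federal states (Bavaria and North Rhine-Westphalia) are recruited". The number of networks in each state is not given.
- **Allocation (Randomisation procedure).** Networks are allocated "under the constraints that the arms contain a similar number of practices", with 4 networks in A and 5 each in B and C. One of 112 admissible allocations is drawn, out of a stated 34,650. State is not among the constraints.
- **Model (Data analysis, Outcome evaluation).** For the within-arm tests: "In the first and second stage, the time (before/after the intervention) is included as fixed effect". The random part is: "A random intercept will be included for patients and for practices". For the arm comparisons: "For the comparisons in the third stage, the intervention group will be included as fixed effect additionally". The covariates are: "Furthermore, age and gender will be included as covariates". No group-by-time term, state term or network term is named.
- **Stage-three hypothesis (Sample size calculation).** "the hypotheses of no difference between the post rates of groups A and B as well as groups B and C will be tested". The Outcome evaluation section names A versus C, not B versus C, as the second contrast. The point below applies to whichever arm contrasts are tested and is worked for A-B and A-C.

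**The concern.** Federal state is fixed before allocation, cannot be changed by the programmes, and is known for every record because eligibility is defined by insurance with AOK in one state or the other. With only 4, 5 and 5 networks per arm and no constraint on state, the two states can easily be spread unevenly over the arms.

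Whether that matters depends on the contrast. A comparison of changes from baseline would largely cancel a constant difference in prescribing level between states. A group main effect does not, because it reflects the level in each arm. The practice random intercept does not help either: it describes variation between practices but does not remove a shift in the arm mean caused by a different mix of states.

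At stake is the interpretation of stage three, where the enriched programmes are compared with the standard set on a planned difference of only 5 points.

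**Working it through.** **1. The planned contrast.** The sample size section expects post rates of 50% in A and 45% in B and C: 5 points, or an odds ratio of (0.45/0.55)/(0.50/0.50) = 0.82.

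This contrast drives the sample size. A two-sided test at 2.5% with 80% power and a 2:1 ratio needs 1,423 in B (or C) and 2,846 in A. The design effects are 1 + 79 × 0.05 = 4.95 and, assuming two cases per patient, 1 + 1 × 0.7 = 1.7. Their product is 8.415, which gives 11,975 and 23,949, against the stated 11,967 and 23,933.

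**2. Imbalance of states over arms.** Assumptions: k of the 14 networks lie in the smaller state, networks are of equal size, and the 4/5/5 allocation is otherwise free. With a, b and c of the k networks falling in A, B and C:

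P(a, b, c) = C(4,a) × C(5,b) × C(5,c) / C(14,k), and the difference in state share is d = a/4 − b/5.

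Worked case, k = 2, C(14,2) = 91:

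| (a, b, c) | ways | absolute d |
|---|---|---|
| (2,0,0) | 6 | 0.50 |
| (0,2,0) | 10 | 0.40 |
| (0,0,2) | 10 | 0 |
| (1,1,0) | 20 | 0.05 |
| (1,0,1) | 20 | 0.25 |
| (0,1,1) | 25 | 0.20 |

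Mean absolute d = (3 + 4 + 0 + 1 + 5 + 5)/91 = 18/91 = 0.198. By symmetry, A-C is the same.

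**3. Error in one contrast.** Multiply by an assumed state gap in prescribing level:

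| k | mean absolute d | points at 5-point gap | points at 10-point gap | chance of ≥ 2.5 points (gap 5 / gap 10) |
|---|---|---|---|---|
| 2 | 0.198 | 1.0 | 2.0 | 7% / 40% |
| 3 | 0.231 | 1.2 | 2.3 | 12% / 45% |
| 4 | 0.256 | 1.3 | 2.6 | 16% / 49% |
| 5 | 0.273 | 1.4 | 2.7 | 18% / 51% |
| 6 | 0.282 | 1.4 | 2.8 | 19% / 52% |
| 7 | 0.284 | 1.4 | 2.8 | 20% / 52% |

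At a gap of zero, every entry in points is zero.

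**4. What the model would report.** Suppose the programmes do not differ, the lower-prescribing state makes up 25% of A and 60% of B (share difference 0.35), and the post rate in A is 50%. The rate in B is then lower by 0.35 × gap:

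- gap 5: 48.25%, odds ratio 0.4825/0.5175 = 0.93
- gap 10: 46.50%, odds ratio 0.4650/0.5350 = 0.87
- gap 15: 44.75%, odds ratio 0.4475/0.5525 = 0.81

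A logistic model with time and group, fitted to expected rates without random effects, gives the same three values. Adding state returns 1.00 in each case. A group-by-time contrast without state also returns 1.00.

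**5. Limits of step 2.** Free 4/5/5 allocation of 14 networks has 14!/(4!5!5!) = 252,252 outcomes. The stated 34,650 equals 12!/(4!4!4!), so the draw described is not the one enumerated here, and only 112 outcomes were admissible. Network sizes are not given, so the actual distribution of state imbalance cannot be derived.

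**The case against.** The strongest reply is that a condensed article need not list every covariate. A detailed analysis plan is announced, and the text does not say that age and gender are the only adjustments. State was not a stratification factor, so no rule that analysis must follow design is broken. No passage says prescribing differs between the two states, and the Discussion already concedes that the small number of allocated units leaves room for bias.

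Part of this stands. The size rests on two figures the article does not give, and an analysis plan could add the term. But the article does set out the confirmatory model term by term, and as written nothing in it removes a state difference from the arm contrast. Acknowledging the small number of units does not change that.

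A reader might infer more than the document supports:

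- *Systematic bias.* The signed imbalance averages zero over free allocations. This is chance imbalance in the one allocation realised.
- *A larger shift.* Taking the worse of A-B and A-C gives a mean share difference of 0.29 to 0.38, or 1.4 to 1.9 points at a 5-point gap. That describes the worse of two contrasts, not a given contrast.
- *The pre/post tests.* Each arm keeps its own networks, so state imbalance between arms does not touch stages one and two.
- *Calendar quarter.* All arms share one calendar, so quarter gives no systematic error in the arm contrasts if case mix by quarter is similar. It could bias the pre/post tests only if the two periods covered different seasons, which no passage shows.
- *The matched comparison clusters.* These belong to a separate analysis, and nothing here shows that they must be formed within state.

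**Conclusion.** The point holds for stage three only. The arm comparison is a level comparison adjusted for age and gender, and allocation is not constrained on state, so a state difference in prescribing level would enter the A-B and A-C contrasts.

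Under the assumptions of equal network sizes, free 4/5/5 allocation and 2 to 7 networks in the smaller state, the average absolute error in one contrast is 20 to 28% of the state gap. That is a fifth to just over a quarter of the planned 5 points if the gap is 5 points, about two fifths to just over half if it is 10, and nothing if there is no gap. Neither the gap nor the networks per state is documented, so these are conditional sizes, not estimates for this trial.

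The model change is worth making because the covariate is fixed before allocation, already in the data and nearly free to include.

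**What to change.** Prespecify federal state as a fixed effect in the stage-three logistic mixed models, alongside time, group, age and gender.

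The cost is a wording change and one degree of freedom at network level, out of 14 networks. The sample size is unchanged.

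The change removes one source of between-network difference. It does not replace a network effect: network is the randomised unit and has no term in the model, so standard errors would still not reflect the remaining variation between networks. Nor does it replace a baseline-adjusted (group-by-time) contrast, which would largely cancel a constant state gap.
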